**6. Case allocation**

It plans to assign the cases to each research center as follows:

| **Research Center** | **Patients for initial treatment**  **(test group: control group)** | **Patients treated with metformin**  **(test group: control group)** |
| --- | --- | --- |
| China Academy of Chinese Medicial Sciences Guang’anmen Hospital | 16:16 | 16:16 |
| Shanghai University of Traditional Chinese Medicine Yueyang Hospital of Integrated Traditional Chinese and Western Medicine | 16:16 | 16:16 |
| The First Affiliated Hospital of Guangzhou University of Traditional Chinese Medicine | 16:16 | 16:16 |
| Beijing University of Traditional Chinese Medicine Dongfang Hospital | 10:10 | 10:10 |
| The Third Affiliated Hospital of Peking University of Traditional Chinese and Western Medicine | 16:16 | 16:16 |
| Peking University People’s Hospital | 16:16 | 8:8 |
| Peking University First Hospital | 6:6 | 6:6 |
| Shanghai Jiaotong University Ruijin Hospital | 6:6 | —— |
| Zhongshan University Sun Yai-sen Memorial Hospital | 12:12 | 6:6 |
| Sichuan University West China Hospital | 12:12 | 18:18 |
| General Hospital of PLA Second Artillery | 8:8 | 8:8 |
| The Central Hospital of China Aerospace Corporation | 8:8 | 16:16 |
| The First Affiliated Hospital of Chongqing Medical University | 14:14 | 14:14 |
| The First Hospital of Hebei Medical University | 14:14 | 20:20 |
| China Meitan General Hospital | 12:12 | 12:12 |
| The Second Xiangya Hospital of Central South University | 6:6 | 6:6 |
| The Second Affiliated Hospital of Chongqing Medical University | 6:6 | 6:6 |
| Nanjing Hospital of Traditional Chinese Medicine | 6:6 | 6:6 |
| **Total** | 200:200 | 200:200 |

## V. Case selection criteria

**1. Inclusion criteria**

1.1 Patients with type 2 diabetes;

1.2 Belonging to TCM Syndrome of dual deficiency of *qi* and *yin*;

1.3 Aged 21～70 years;

1.4 Patients for initial treatment: Patients who have not received any hypoglycemic agent and are non-obese,, with body mass index (BMI) within 18kg/m2 ~ 28 kg/m2 (not included);

1.5 Patients treated with metformin: Patients have received treatment with metformin (immediate-release) at a stable dose ≥ 750 mg/day for at least 3 months before screening, with body mass index (BMI) within 18kg/m2 ~ 35 kg/m2 (not included);

1.6 Body weight remains constant (body weight fluctuates by less than 10% within at least 3 months before screening);

1.7 Poor glycemic control, fasting blood glucose greater than 126 mg/dl (7.0 mmol/L) and HbA1c >7.0% (preliminary screening), fasting blood glucose greater than 126 mg/dl (7.0 mmol/L) (after run-in);

1.8 Patients still meet the above criteria (without considering HbA1c) after a 4-week run-in period.

**2. Exclusion criteria**

2.1 Personnel of the research base who have a direct relationship with this study, as well as their close relatives. Close relatives refer to the spouse, parent, child, brother or sister, whether due to blood relationship or legal adoption.

2.2 Employees of Guangzhou Zhongyi Pharmaceutical Co., Ltd. (including staff, temporary contractual workers or designated personnel participate in this study.)

2.3 Have participated in this study in the past or other studies using sulfonylureas.

2.4 Participated in intervention medical, surgical or pharmacological research (research that gives study drugs, medical or surgical therapy) within 30 days before screening. This standard includes drugs that have not been approved by drug administration departments when entering the study.

2.5 Women of childbearing age who meet the following conditions (not yet received surgical contraception and are at the stage from menarche to 1 year after menopause):

1) Lactating women.

2) Positive pregnancy test results at the enrollment.

3) Plan to get pregnant during the research.

4) Did not take effective birth control measures within 3 months before screening.

5) Patients do not agree to continue the use of effective birth control means in the process of the trial, as determined by the investigators.

2.6 Fasting blood glucose ≥ 13 mmol/L, or HbA1c ≥ 11%.

2.7 Have more than 3 episodes of severe hypoglycemia within 6 months before the screening.

2.8 Those that who are allergic to sulfonylureas or their ingredients.

2.9 With contraindications of using metformin or sulfonylureas according to the drug package insert.

2.10 Had received treatment with exogenous insulin for more than 1 week within 3 months before screening.

2.11 Those who have a history of clinically significant heart disease within 1 year before entering the study, or with active heart diseases including myocardial infarction, severe arrhythmia, unstable angina, moderate or severe heart failure (New York Heart Society cardiac function grading: class III or IV), coronary artery bypass surgery or reconstructive vascular operation, or those who are estimated to require coronary artery bypass surgery or reconstructive vascular operation during the study.

2.12 Patients who have a history of kidney transplant or are currently receiving dialysis treatment or with serum creatinine levels reaching the upper limit of normal value.

2.13 With obvious clinical signs or symptoms of liver disease, acute or chronic hepatitis, or alanine aminotransferase (ALT or AST) greater than 2.5 times the upper limit of normal value.

2.14 Suffering from hemoglobin disease or chronic anemia.

2.15 Suffering from active proliferative kidney disease.

2.16 Patients who are receiving any of the following medications are to be excluded:

1) Have used thiazolidinediones (TZD) within 3 months before screening.

2) Have used insulin secretagogue (sulfonylureas or nateglinide) within 1 month before screening.

3) Have used α-glucosidase inhibitors (such as miglitol or acarbose) within 1 month before screening.

4) Drugs that directly affect the gastrointestinal motility including metoclopramide and cisapride, and long-term use of macrolide antibiotics, but not limited to these drugs.

5) Systemic glucocorticoid treatment (not including local or inhaled medication) by oral administration, intravenous (IV) or intramuscular (IM) injection on a regular basis (more than 1 month) or within 1 month before screening.

2.17 Suffering from active or untreated malignancy, or malignancy in clinical remission less than 5 years (except for basal cell carcinoma or cutaneous squamous cell carcinoma, cervical carcinoma in situ, or prostate carcinoma in situ).

2.18 With a history of organ transplantation.

2.19 With a present or past history of drug or alcohol abuse that may lead to poor compliance of subjects as determined by the investigators.

2.20 For any other reason, the investigators consider it inappropriate to participate in this study.

**3. Withdrawal criteria**

3.1 After inclusion, the patient is found to not meet the inclusion criteria or meet the exclusion criteria.

3.2 Patients have not received any medication after inclusion for various reasons.

3.3 Patients without any record.

**4. Loss criteria**

4.1 Definition: All subjects who have completed the informed consent, been determined as eligible through screening in the run-in period and have been randomized into the trial, are considered as loss cases as long as if they do not complete the observational period specified in the protocol, no matter at any time and due to any reason.

4.2 Treatment of loss cases

4.2.1 When the subjects are lost, the investigators should contact the subjects as far as possible to inquire about the reasons, record the last medication time, and complete the evaluation items that can be completed.

4.2.2 When the subjects withdraw from the trial due to allergic reactions, adverse reactions, or treatment failure, the investigators should take appropriate therapeutic measures according to the actual situation of the subjects.

**5. Termination (withdrawal)**

In the following situations, the study will be terminated for the patients, but the patients will be included in the FAS statistics:

5.1 If the female patient gets pregnant (violation to the protocol).

5.2 If the patient has not used the study drugs (including metformin) in accordance with therequirements of the protocol for more than 7 consecutive days.

5.3 If the patient has used insulin for more than 7 days, or month than 7 days within 1 month.

5.4 If the patient has used combined therapy with the drugs that should be excluded for more than 7 days.

5.5 If the patient’s (finger whole blood) fasting blood glucose has been greater than 234 mg/dL (13 mmol/L) for 3 consecutive times (lack of efficacy).

5.6 Serious adverse events occur.

5.7 If the patient has recurrent hypoglycemia (more than 2 episodes of hypoglycemia per week in 4 consecutive weeks), especially severe hypoglycemia (more than 2 episodes of severe hypoglycemia within 30 days), the investigator must consider terminating the trial for the patient.

If the investigators determine the patients should withdraw from the trail because of serious adverse events or significantly increased clinical laboratory parameters, appropriate measures should be taken immediately and the principal of the study should be notified.

The investigators terminate the trial or terminate the patients to participate in the trial for any reason; those patients under early termination will continue to carry out the visit procedures for early termination as specified in the protocol procedures.

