## III. Trial endpoints

**1. Primary endpoint**

The primary endpoint of this study is the change in HbA1c levels at 48 weeks from baseline, compared between the treatment groups.

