## IV. The overall design of the trial

**1. Sample size**

The sample size of the trial is designed and estimated according to non-inferiority test. The assumption of non-inferiority test is that the Xiaoke pill is not inferior to glibenclamide in terms of reducing HbA1c. Xiaoke Pill was regarded as non-inferior to treatment with Glibenclamide only if, after 48 weeks of treatment, the upper limit of the two-sided 95% CI for the difference in mean HbA1c change was less than 0.4%. A sample size of 400 patients was estimated to provide more than 90% power to test the hypothesis that Xiaoke Pill treatment was non-inferior to treatment with Glibenclamide in each of the study groups, assuming a 20% early discontinuation rate, and an expected inter-patient SD of 1.1%. The sample size estimation is based on being able to provide sufficient amount of information.

According to statistical results of sample size, in order to better guide the clinical application of Xiaoke Pills to improve the effectiveness of medication, this study is plan to enroll 400 non-obese patients with type 2 diabetes who have not received any antidiabetic agents before and have unsatisfactory glycemic control on diet and exercise and 400 patients with type 2 diabetes who have unsatisfactory glycemic control after treatment with metformin alone for over 3 months. 800 patients will be randomly assigned to the treatment groups and control group.

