**2. Design of the trial**

This study is a randomized, double blind and double dummy, masculine parallel comparison, multi-center clinical trial.

It is estimated that a total of 1600 type 2 diabetes patients with unsatisfactory glycemic control will participate in preliminary screening, of which 800 patients have not used any hypoglycemic agents and are non-obese (hereinafter referred to patients for initial treatment), and 800 patients have unsatisfactory glycemic control after treatment with metformin alone for over 3 months (hereinafter referred to patients treated with metformin). After determined as eligible through preliminary screening, about 1,000 patients (each 500 of patients for initial treatment and patients treated with metformin) will enter the four-week run-in period. During the run-in period, it will maintain the same normal dose of metformin for patients treated with metformin, in addition to diet and exercise management.

After the end of run-in, those who still meet the inclusion criteria (a total of 800 patients, including each 400 in the initial treatment group and metformin treatment group) will be randomly divided into the test group and control group, i.e., Xiaoke Pills group and glibenclamide group (n = 400 patients). In the glibenclamide group, the initial dose is glibenclamide 1.25 mg (0.5 tablets) with simulator of Xiaoke Pills 5 pills, once daily, and the maximal dose is glibenclamide 7.5 mg/d for oral administration in 3 times; in the Xiaoke Pills group, the initial dose is Xiaoke Pills 5 pills with simulator of glibenclamide tablets 1.25 mg (0.5 tablets), once daily, and the maximal dose is Xiaoke Pills 30 pills/d for oral administration in 3 times. Each subject will be followed up for 48 weeks, and the necessity for dose adjustment will be evaluated every 4 weeks according to fasting blood glucose levels. If the patient has achieved the Study Termination Criteria of the clinical trial, then the trial is terminated and transferred to conventional treatment, while the treatment methods comply with the “China Guidelines for Diabetes Prevention and Treatment”.

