**4. Items to be followed-up every 12 weeks**

4.1 fasting insulin, C peptide, glycosylated hemoglobin (HbA1c);

4.2 lipids, inflammatory factors (hsCRP), adiponectin;

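### Patients terminated under V.5 stay in the analysis of 48-week HbA1c, but no week-48 value is collected from them and the early-termination visit the protocol cites is not in its schedule

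*Protocol*

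**What the plan says.** - **Endpoint and margin.** Section III.1 makes the primary endpoint "the change in HbA1c levels at 48 weeks from baseline". Section IV.1 accepts non-inferiority if "the upper limit of the two-sided 95% CI for the difference in mean HbA1c change was less than 0.4" percentage points, and sizes the trial "assuming a 20% early discontinuation rate".
- **Analysis set.** Section XII.1 bases efficacy on the ITT population: every randomised patient who took at least one dose.
- **Termination.** Section V.5 lists seven grounds (5.1 to 5.7) on which the study ends for a patient, and says that these patients still count in the FAS. Ground 5.5, repeated fasting glucose above 13 mmol/L, is labelled as lack of efficacy. The section then states that "those patients under early termination will continue to carry out the visit procedures for early termination as specified in the protocol procedures".
- **Hyperglycaemia failures.** The Study Termination Criteria in section III withdraw these patients from the study, not only from study drug. Section IV.2 repeats this: "If the patient has achieved the Study Termination Criteria of the clinical trial, then the trial is terminated and transferred to conventional treatment".
- **Loss cases.** Under V.4, randomised patients "are considered as loss cases as long as if they do not complete the observational period specified in the protocol", whatever the reason. V.4.2 asks investigators to "complete the evaluation items that can be completed".
- **HbA1c schedule.** Section IX.4, headed "Items to be followed-up every 12 weeks", and the trial-procedures table place HbA1c at weeks 12, 24, 36 and 48 after baseline. The table has visits 1 to 14 (week -4 to week 48) and no other column.

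**The concern.** The protocol requires terminated patients in the primary analysis and also ends the visits that would supply their primary outcome. Its one safeguard, a set of early-termination procedures, is a cross-reference whose target is in neither the procedures table nor section IX. V.4.2 is the nearest substitute, and it names neither HbA1c nor week 48.

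Part of the loss depends on glucose by rule (5.5 and the Study Termination Criteria), so it cannot be assumed unrelated to the outcome. Unequal failure between arms is also something the trial sets out to examine: goal 2.4 in section II asks whether Xiaoke Pills lower the risk of secondary sulfonylurea failure relative to glibenclamide. With a margin of 0.4 points, it matters whether the conclusion rests on observed week-48 values or on assumptions about about a fifth of the patients.

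**Working it through.** **1. The plan's own figure.** Inputs from IV.1: margin 0.4, SD 1.1, two-sided 95% CI, power above 90%, 20% discontinuation. I read the 400 as applying to each of the two strata, 200 per arm. I assume a true difference of 0, which the protocol does not state as a number.

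- n per arm = 2 × (1.960 + 1.282)² × 1.1² / 0.4² = 159 after rounding up.
- Allowing for 20% loss: 159 / 0.80 = 199 per arm, 398 in total, against 400 stated. The figure reproduces.
- Power with 160 per arm: SE = 1.1 × √(2/160) = 0.123; Φ(0.4/0.123 − 1.96) = 90.2%.
- Power with all 200 per arm: SE = 0.110; 95.3%.

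Both powers exceed 90%. The match of 199 to 200, together with the stated discontinuation allowance, indicates that discontinuers were counted as giving no primary value. That is 40 of 200 per arm in each stratum, or 0.20 × 800 = 160 patients overall.

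**2. Age of the last HbA1c.**

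- Ground 5.5 has no dose condition. A patient terminated at week 20 has a last scheduled HbA1c from week 12, 8 weeks earlier. Just before week 24 the gap is nearly 12 weeks. Before week 12 only baseline exists.
- The Study Termination Criteria apply only at the top dose. By IV.2 and VI.5 the dose rises from 5 to 30 pills in (30 − 5)/5 = 5 steps of 4 weeks, so week 20 is the earliest. The first fasting glucose on that dose is at week 24, when HbA1c is also drawn, so the fastest titrators have a recent value. Patients who fail later can fall between two draws.
- In neither case is there a value at week 48.

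**3. Possible shift in the treatment difference.** Let m be the share missing in an arm and D the amount by which the mean change of unobserved patients is worse than that of observed patients. The full-arm mean is then the observed mean + m × D. With the same D in both arms, the difference between arms shifts by D × (m_test − m_control). All values of m and D below are assumptions; only the 20% average comes from the protocol.

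| Missing, test v control | D = 0.5 | D = 1.0 | D = 1.5 | D = 2.0 |
|---|---|---|---|---|
| 20% v 20% | 0 | 0 | 0 | 0 |
| 22% v 18% | 0.02 | 0.04 | 0.06 | 0.08 |
| 25% v 15% | 0.05 | 0.10 | 0.15 | 0.20 |

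Reversing the two percentages reverses the sign.

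**4. What a shift would do to the error rate.** If the true difference equals the margin and the unobserved data hide a shift b in favour of the test arm, the chance of declaring non-inferiority in one stratum is Φ(b/0.123 − 1.96). For b = 0, 0.05, 0.10 and 0.20 this is 2.5%, 6%, 13% and 37%.

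**The case against.** **The protocol does ask for an exit assessment.** V.5 and V.4.2 both do, so it would be wrong to infer that nothing is collected at exit. This stands: the defect is that the content is unspecified. Nor can one say that the procedures exist nowhere. The contents list a Notice ahead of the trial procedures that is not visible in full here. What can be said is that they are in neither the procedures table nor section IX.

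**The missing patients are not simply those who did worst.** A reader might infer that from V.5, but only 5.5, with the Study Termination Criteria, is efficacy failure. The other grounds include pregnancy, non-adherence and recurrent hypoglycaemia, where HbA1c may be low, and 5.7 requires only that the investigator consider termination. This stands; glucose failure is one rule-based part of the loss.

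**The direction of bias is not shown.** A reader might infer that carrying earlier values forward must favour non-inferiority. The documents do not support that. An early value during titration reflects a lower dose and can be worse than a later one, and the net effect depends on unknown differences between arms. A large shift is also not documented. With 20% loss in both arms, it would take a 2.0-point gap between the arms' unobserved patients to reach 0.4 (0.20 × 2.0). Both arms receive matched glibenclamide doses (5 × 0.25 mg = 1.25 mg to start) titrated to the same fasting glucose range.

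**Missing data belong to the SAP.** An SAP can choose a method, but it cannot supply week-48 values that were never drawn. This part of the objection fails.

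**Week-48 values after conventional treatment can themselves dilute a difference.** This stands, and it shapes the fix.

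**Conclusion.** The point holds as a gap in data collection. Terminated patients are kept in the analysis of 48-week HbA1c change, the protocol ends their scheduled observation, and the procedures it relies on at exit are not in its schedule. The data cannot be recovered later, whatever the SAP says.

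Its documented size is the planned 20%, about 160 of 800 patients. That is a planning allowance, not a known count. The effect on the result is unknown in sign and size. Under the assumed scenarios it runs from 0 (equal loss, equal severity) through 0.02 to 0.08 (22% v 18%) to 0.05 to 0.20 (25% v 15%), against the 0.4 margin. The documents do not support a claim that the plan is biased towards non-inferiority. They support the narrower claim that the plan leaves the question open when a cheap measurement would largely settle it.

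**What to change.** No stopping or rescue rule needs to change.

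1. Add an early-termination column to the trial-procedures table and a matching item to section IX, with central-laboratory HbA1c and FPG drawn at the termination visit without delaying care.
2. Reword V.5, and align section III, IV.2 and V.4, so that the listed events end study drug but not observation. Collect central-laboratory HbA1c at week 48 from every randomised patient unless consent is withdrawn.
3. State that the week-48 value enters the primary ITT analysis and the termination-visit value enters a supportive on-treatment analysis.
4. Reconcile two wordings in the same text. The Study Termination Criteria and ground 5.5 differ on the number of consecutive readings above 13 mmol/L (2 v 3). V.5 refers to an FAS, while XII.1 defines only ITT and PPS.

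**Cost:** one or two extra blood samples for about 160 patients at the planned rate, a schedule column and a consent line. If every week-48 value were obtained, power per stratum would rise from 90.2% to 95.3%, provided a zero difference and an SD of 1.1 also hold in the full randomised set.

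**Downside:** week-48 values taken after conventional treatment may dilute a real difference, which matters in a non-inferiority trial. The supportive on-treatment result should therefore be reported beside the primary one.

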**6. Subject selection procedures**

Type 2 diabetes patients of initial treatment or irresponsive to metformin therapy who have visited the units participating in the study for a long term, if determined to meet the inclusion criteria through routine examination, they can enter the run-in period. Before screening, it should inform the patients the content, benefits and possible risks of the clinical trial in accordance with the principles of GCP, only when the informed consent is obtained from the patients with their signature, it can perform screening on the patients and let the patients enter the run-in period.

## VI. Dosage regimens

**1. Study drugs**

**Investigational drug**: Xiaoke Pills (each pill contains glibenclamide 0.25mg + Chinese herbs), produced by Guangzhou Zhongyi Pharmaceutical Co, Approval Document Number: SFDA (approved) Z44020045, production batch number: K03300, shelf life: 3 years.

**Control drug:** glibenclamide tablets, 2.5 mg/tablet, produced by Tianjin Pacific Pharmaceutical Co., Ltd., Approval Document Number: SFDA (approved) H12020790, production batch number: 070708, shelf life: 3 years.

**Simulators:** The simulator of Xiaoke Pills and simulator of glibenclamide tablets are prepared in line with the requirements for placebo preparation, which are pills or tablets not containing any active ingredient.

**Basic medication** (patients treated with metformin): metformin hydrochloride tablets, 0.25 g/tablet, purchased by the Guangzhou Zhongyi Pharmaceutical Co., Ltd., Approval Document Number: SFDA (approved) H11020976, shelf life: 3 years.

In order to ensure the implementation of the blindmethod, the study drugs of the trial will be divided into No.1 medication and No.2 medication. No.1 medication includes Xiaoke Pills and simulator of Xiaoke Pills, while No.2 medication includes glibenclamide tablets and simulator of glibenclamide tablets.

